## Methods

The study (a) will be registered in ClinicalTrials.gov, which is the largest registry of clinical trials and is administered by the United States National Library of Medicine (NLM) at the National Institutes of Health, and (b) will be conducted and reported according to CONSORT guidelines (46).

### Design and Setting

The study will be conducted as a parallel randomized controlled study in various outpatient alcohol treatment clinics in Denmark. Most individuals with AUD who present themselves for treatment at these clinics are offered outpatient treatment. This outpatient treatment is financed through public funds. It accepts self-referrals, and patients can remain anonymous during treatment. Only treatment for alcohol problems is provided at the outpatient clinics.

### Primary Treatment at the Outpatient Alcohol Clinics

At treatment entry, patients will be offered detoxification, if needed, before their primary treatment at one of the outpatient clinics is initiated. The primary treatment lasts 3 months and consists of both a pharmacological and a psychological treatment. The pharmacological treatment includes treatment with disulfiram and acamprosate. Naltrexone or nalmefene is also offered when deemed appropriate. The psychological treatment consists of cognitive-behavioral therapy (CBT), which is provided during hour-long individual or group sessions and typically includes eight sessions. The therapist and patient jointly plan the course of the patient's treatment. The treatment typically includes psychoeducation, functional analysis of drinking situations, and the development of coping strategies. The strategies include waiting out until an urge passes rather than acting on it, thinking about the negative consequences of drinking, thinking about the positive consequences of sobriety, consuming healthy alternative foods and beverages, problem-solving, and homework assignments between sessions. Therapists conduct the psychological treatment; they include nurses and social workers who have been specifically trained to deliver the range of therapies. Supervision takes place frequently, and psychiatrists regularly monitor patients' progress during the treatment (47).

### Recruitment

Based on a power calculation (see Section 2.7.), a total of 317 patients will be required for the data analysis. On the basis of data from the Danish National Alcohol Treatment Register (48) and prior studies conducted at this clinic (49–52) and prior studies of AACTP (32, 36, 42), it seems feasible that at least 317 eligible patients (see Section 2.4.) can be recruited from January 2021 to July 2022.

After completing detoxification and prior to starting primary treatment, each patient will be briefly informed about the project and asked whether he or she is willing to meet with a research assistant who will provide further information about the study. If the patient agrees, the research assistant will provide the patient with oral and written information about the details of the study. After informed consent has been provided, a baseline interview will be conducted, and each patient meeting the eligibility criteria will be randomized. To minimize the risk of bias and to overcome potential group imbalances, the current study will utilize an urn technique that will randomize the patients to one of the three treatment groups.

### Eligibility Criteria

To be eligible to participate, patients must fulfill the following criteria. They must (1) sign written informed consent, (2) be between 18 and 65 years old (because the intervention is web-based), (3) be fluent in Danish, (4) have completed detoxification (if deemed appropriate), (5) have been admitted to primary treatment within the past 8 weeks, (6) not be color-blind, (7) not have a severe psychiatric or neurological illness (e.g., a psychotic disorder, intellectual disability, dementia) or terminal physical illness.

### Experimental and Control Groups

The 317 patients (see power analysis below) fulfilling the eligibility criteria will be randomized to one of the three groups: Group A: AACTP delivered *via* a smartphone application + treatment as usual (TAU; *n* = 106), Group B: ACTP sham training delivered *via* a smartphone application + TAU (*n* = 106), or Group C: TAU only (*n* = 106). Patients in Group A will receive seven sessions of AACTP (one session per week for 7 weeks). Patients in Group B will receive seven sessions of sham training (one session per week for 7 weeks). Patients in Group C will receive only the primary treatment for AUD. Patients in the AACTP and sham control groups will start the primary treatment within the 1st month of their admission, so that the add-on treatment will not extend beyond the 3-month treatment period.

#### Attentional Control Training Program *via* a Smartphone Application

The AACTP, which is delivered *via* a smartphone application and based on an Android application, was designed in accordance with the conventional AACTP to help drinkers become aware of the automatic cognitive aspects of their alcohol use. The stimuli comprise alcohol-related pictures and non-alcohol-related pictures and are individually presented on a computer screen in a random order. If patients need it, a research assistant in the treatment facility will assist them with the installation of the application on their smartphone. The installation of the application on patients' personal smartphone will allow them to complete the training program at home. Thus, they will not be constrained by having to use the application in the outpatient facility.

The AATCP training will consist of seven sessions, each of which takes 10–15 min to complete. Each session will start with practice with individual stimuli (i.e., Levels 1 and 2 in the original AACTP) and proceed to Level 3, in which the patient will be asked to either (a) identify the green outline color of a non-alcohol-related picture, while ignoring the red outline color of the alcohol-related picture presented adjacent to it (stimulus-irrelevant version), or (b) identify the picture with non-alcohol-related content, while ignoring the picture with alcohol-related content presented adjacent to it (stimulus-relevant version). Level 3 is the most difficult and most effective level in the conventional AACTP. It is defined as the level in which the patient is trained to divert his or her attention away from alcohol cues when both an alcoholic and a non-alcoholic stimulus is present, and they compete for the patient's attentional resources. The patient should respond by touching the non-alcohol stimulus on the screen as fast and accurately as possible. During the sessions, the speed at which the stimuli are presented systematically increases, while the width of the outlines decreases and gradually fades away in the final sessions. This increases the difficulty of the task and trains the person's attentional system so that the alcohol-related stimuli are ignored even when there is no color cue. In case the patient makes a mistake and touches the incorrect stimulus, the tablet will provide an auditory-visual alert.

The training, therefore, occurs in seven hierarchical steps, which are arranged according to an increasing level of difficulty. Prior to each session, the patient will be encouraged to set a goal for decreasing his or her reaction times (RTs) to the neutral, non-alcohol-related stimuli, which requires increasing efficiency for the distracting cues to be ignored. The goal will be for each participant to improve his or her attentional control until a performance plateau has been reached (RTs < 1,000 ms with a response accuracy > 90%).

After completing each session, the participant will be given numerical/graphical feedback on (a) the number of errors made and the mean RTs to the non-alcohol-related stimuli, and (b) a brief auditory/written interpretation of the results. The aim of the training will be to motivate patients to actively take part in the program in a meaningful and goal-directed way. Although the conventional AACTP includes some gamification elements, the smartphone application includes additional gamification elements, such as time-pressure, sound-effects, hierarchical levels, feedback, achievement ranking, and competition. These elements serve to increase the patient's engagement and compliance. Also, to increase engagement and the chances of obtaining a dose-response effect across participants, the application can control for the number of practice sessions that each trainee can complete in each period, and it can automatically save and securely encrypt and send the training data to the research server *via* an internet connection.

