#### Attentional Control Training Program Sham Training *via* a Smartphone Application

The AACTP sham control training is like the AACTP in that it is delivered *via* a smartphone application based on an Android or iOS application and is designed in accordance with the conventional program. Patients receiving the sham control program will also have the application installed on their personal smartphone. They, therefore, will be able to use the program in any location that they wish. However, different from the AACTP, patients in the active control group will be trained to direct their attention toward the non-alcohol-related stimuli on only 50% of the trials. On the remaining trials, their attention will be directed toward the alcohol-related stimuli. Thus, the sham training should counteract the induction of AB with AB re-training because the allocation of the participant's attention will distribute equally between the alcohol-related and the non-alcohol-related stimuli. The patient will respond by touching the circle displayed on the computer screen as quickly and accurately as possible. Like the ACTP training, a red outline will signal a stimulus that should be ignored, and a green outline will signal a neutral stimulus, which should be responded to, but the alcoholic or non-alcoholic stimuli will appear equally often with the red or green outline. Also, throughout each session, the speed at which the stimuli are presented will systematically increase, and the width of the outlines will decrease and gradually fade away in the final sessions, thereby increasing the difficulty of the task. In case the patient makes an error and touches an incorrect stimulus, the tablet will provide an auditory-visual alert. As in the smartphone version of the alcohol ACTP, prior to each session the participant will be encouraged to set a goal for the speed of the reaction times and the number of errors made until his or her performance plateau has been reached. After completing each session, the patient will be given both graphical and auditory feedback. Hence, the program will contain all the same features as the smartphone version of the alcohol ACTP. The only difference is that the patient's attention will be equally guided toward non-alcohol-related and alcohol-related stimuli in the sham control version. Selected practice data will be sent to the server to control for dose-response effects. Having the sham condition is important for ensuring that effects obtained with the smartphone version of the alcohol ACTP result from the re-training of the patients' alcohol attentional bias and not from the additional attention that they receive or from some other unintended effect, such as the Hawthorne effect (53).

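### Both apps run on the patient's own smartphone, but eligibility requires no usable phone, and the protocol describes the active app's platform in two incompatible ways

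*Protocol article*

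**What the plan says.** All of this is in the Methods of the protocol article.

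- **Device.** For the active app: "The installation of the application on patients' personal smartphone will allow them to complete the training program at home". For the sham: "Patients receiving the sham control program will also have the application installed on their personal smartphone". Staff help with installation is offered for the active app, but no section says that a phone will be lent or supplied. In both app descriptions the error alert is said to come from a tablet.
- **Platform.** The section on the active app says it is delivered via "a smartphone application and based on an Android application". The section on the sham says that it "is like the AACTP in that it is delivered *via* a smartphone application based on an Android or iOS application". The sham section adds that the two programs share all features and differ only in where attention is guided.
- **Eligibility.** Seven criteria are listed as those a patient must fulfil. None mentions a smartphone or an operating system. The one reference to delivery is the reason given for the age limit: patients must "be between 18 and 65 years old (because the intervention is web-based").
- **Randomisation.** Under Recruitment, "each patient meeting the eligibility criteria will be randomized".
- **Analysis.** The Statistical Analysis section commits to intent-to-treat. The Aims add a hypothesised dose-response effect within Group A.

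**The concern.** Eligibility screens for some things that bear on the ability to do the training: colour-blind patients are excluded, and the age limit is justified by the mode of delivery. It does not screen for the one thing without which the training cannot be delivered, a phone that runs the app. Patients who lack one are therefore randomised, and two of the three arms cannot treat them.

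Three comparisons are exposed.

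- **A versus C** is diluted, because intent-to-treat keeps the untreated patients in A.
- **A versus B** is weakened. If the two apps really run on different platforms, it is also unbalanced, because some patients would be treatable in B but not in A. The sham is there to isolate attentional retraining, and that needs the same access in both app arms.
- **The dose-response analysis in A** would count patients who did no sessions because of their device together with patients who chose not to train. Dose would then partly measure device access.

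**Working it through.** No figure in the protocol depends on this point, so there is none to reproduce. The check is a comparison of the text, followed by the algebra of dilution.

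**1. Who can receive the allocated app.** The platform statements allow two readings.

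| Eligible patient | Reading 1: active app Android only, sham Android or iOS | Reading 2: both apps Android or iOS |
|---|---|---|
| Android owner | A yes, B yes | A yes, B yes |
| iPhone owner | A **no**, B yes | A yes, B yes |
| No usable smartphone | A **no**, B **no** | A **no**, B **no** |

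Group C needs no app under either reading. The last row is the same under both readings, so the missing criterion matters whichever is right. Only the middle row depends on the platform statement.

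**2. Effect on the intent-to-treat contrasts.** Let δA and δB be the mean effects of the active and sham apps, each relative to no app, among patients who receive them. Assume that a patient who receives no app gains nothing from the allocation. Let q be the share with no usable phone and i the share of iPhone owners.

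- A versus C, Reading 2: (1 − q)·δA. Reading 1: (1 − q − i)·δA.
- A versus B, Reading 2: (1 − q)·δA − (1 − q)·δB = (1 − q)·(δA − δB). The contrast is smaller but still compares like with like.
- A versus B, Reading 1: (1 − q − i)·δA − (1 − q)·δB = (1 − q)·(δA − δB) − i·δA. The last term is an imbalance caused by platform alone.

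**3. Scale, for illustration only.** The documents give no share of patients without a smartphone or with an iPhone, so the untreated share is an assumption. Group size is 106, as stated under Experimental and Control Groups. The power column takes a single two-arm comparison set at 90% power with two-sided α = 0.05 and an effect scaled by (1 − q): power = Φ[(1.960 + 1.282)(1 − q) − 1.960]. The sample size needed to restore 90% rises by 1/(1 − q)². Here q is the whole untreated share, whatever the reason.

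| Assumed untreated share | Patients of 106 | Effect retained | Power, from 90% | Sample size multiple |
|---|---|---|---|---|
| 0% | 0 | 100% | 90% | 1.00 |
| 5% | 5 | 95% | 87% | 1.11 |
| 10% | 11 | 90% | 83% | 1.23 |
| 20% | 21 | 80% | 74% | 1.56 |
| 30% | 32 | 70% | 62% | 2.04 |
| 50% | 53 | 50% | 37% | 4.00 |

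For example, at 10%: 3.242 × 0.90 − 1.960 = 0.958, and Φ(0.958) = 0.83. These are not the trial's own power figures. Its planned test is a group-by-time interaction over three groups and four time points.

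**The case against.** The strongest objection concerns platform. A reader might infer that Group A alone loses its iPhone owners while B and C are unaffected. The documents do not establish that. The sham section gives Android or iOS as a respect in which the sham resembles the active app, and it names the direction of attention as the sole difference. The active-app section never says that other systems are excluded. An incomplete sentence there is at least as plausible as a real platform split. Nor are B and C both unaffected where the patient has no smartphone: B cannot treat that patient either.

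Three further points are fair.

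- Any large power loss comes from an assumed ownership share. Under the sham section's wording, the share of iPhone owners left untreated is zero.
- A reader might also infer that sites would drop or replace patients whose app cannot be installed, leaving a platform-selected Group A. Nothing in the text allows this, and intent-to-treat is already stated.
- The device arrangements are less settled than the personal-phone wording suggests. Both app sections mention a tablet, and the Ethics section limits the training to clinic opening hours, which sits awkwardly with training at home. Still, no section offers a study device.

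Lastly, this is a condensed article, and the full protocol may screen for devices. That carries limited weight, because the criteria are presented as the list a patient must fulfil and Recruitment randomises everyone who meets it. The conflict over platform lies within the article itself.

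What stands after this is the missing device requirement and the conflict between the two app descriptions.

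**Conclusion.** The point holds in a limited form. As written, the protocol randomises patients to A or B who may be unable to receive the allocated app, and its two app sections disagree on where the active app runs. The first defect dilutes A versus C, weakens A versus B and mixes device access into the dose-response analysis. The second leaves open whether A and B are affected equally.

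It does not follow that the sham comparison is broken. If both apps run on both systems, A and B are affected alike and their contrast shrinks without becoming unbalanced.

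The size is unknown. The intent-to-treat effect against C falls to (1 − q) of its value, with q to be supplied by the sponsor. The formula assumes that untreated patients gain nothing and would otherwise have had the average effect. Confidence is high for the missing criterion and the inconsistency, and low for the magnitude. This should be fixed, but it does not by itself invalidate the design.

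**What to change.** 1. Add an eligibility criterion, checked before randomisation and identical for all three arms: the patient owns a smartphone on which both study applications can be installed. Applying it to Group C as well keeps the three arms drawn from the same population.
2. Reconcile the two app sections so that both give the same platform list, and correct or explain the references to a tablet. If the active app does exist only for Android, the shared list, and hence the criterion, should be Android for all arms.

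No change to the analysis population is needed, since intent-to-treat is already specified.

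The cost is one eligibility line, one screening question and a wording correction. The trade-off is slightly fewer eligible patients and a conclusion limited to owners of supported phones, who are the only patients that an app on a personal phone can serve.

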#### Attentional Control Training Program Sham Training *via* a Smartphone Application

The AACTP sham control training is like the AACTP in that it is delivered *via* a smartphone application based on an Android or iOS application and is designed in accordance with the conventional program. Patients receiving the sham control program will also have the application installed on their personal smartphone. They, therefore, will be able to use the program in any location that they wish. However, different from the AACTP, patients in the active control group will be trained to direct their attention toward the non-alcohol-related stimuli on only 50% of the trials. On the remaining trials, their attention will be directed toward the alcohol-related stimuli. Thus, the sham training should counteract the induction of AB with AB re-training because the allocation of the participant's attention will distribute equally between the alcohol-related and the non-alcohol-related stimuli. The patient will respond by touching the circle displayed on the computer screen as quickly and accurately as possible. Like the ACTP training, a red outline will signal a stimulus that should be ignored, and a green outline will signal a neutral stimulus, which should be responded to, but the alcoholic or non-alcoholic stimuli will appear equally often with the red or green outline. Also, throughout each session, the speed at which the stimuli are presented will systematically increase, and the width of the outlines will decrease and gradually fade away in the final sessions, thereby increasing the difficulty of the task. In case the patient makes an error and touches an incorrect stimulus, the tablet will provide an auditory-visual alert. As in the smartphone version of the alcohol ACTP, prior to each session the participant will be encouraged to set a goal for the speed of the reaction times and the number of errors made until his or her performance plateau has been reached. After completing each session, the patient will be given both graphical and auditory feedback. Hence, the program will contain all the same features as the smartphone version of the alcohol ACTP. The only difference is that the patient's attention will be equally guided toward non-alcohol-related and alcohol-related stimuli in the sham control version. Selected practice data will be sent to the server to control for dose-response effects. Having the sham condition is important for ensuring that effects obtained with the smartphone version of the alcohol ACTP result from the re-training of the patients' alcohol attentional bias and not from the additional attention that they receive or from some other unintended effect, such as the Hawthorne effect (53).

#### Treatment as Usual

Patients in the Treatment-As-Usual (TAU) (see Section 2.2.) control group will not receive any kind of additional treatment, because we aim to determine whether the smartphone version of the alcohol ACTP will increase the effectiveness of a well-established, evidence-based pharmacological and psychological treatment.

### Measures

Upon admission to the study, patients in all three or the groups will be assessed in a baseline interview. Details about patients' socio-demographic characteristics, AUD diagnosis, treatment goals, and pharmacological treatment will be obtained from their clinical records (54–56). At baseline, the general premorbid intelligence level and cognitive functioning will be assessed. Experimental measures of patients' cue-induced cravings, alcohol AB, action-tendency bias, inhibition bias, and cognitive flexibility (24, 26, 27, 57, 58) will be administered at baseline and post-treatment. Clinical measures of patients' alcohol consumption (the primary outcome measure), cravings, self-efficacy, and affective states (the secondary outcome measures) (57–62) will be taken at the baseline, post-treatment, and follow-up assessments. The follow-ups will be given at 3- and 6-months post-treatment.

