## Abstract

**Background:** There is consistent evidence that community and clinical samples of individuals with an alcohol use disorder (AUD) have attentional biases toward alcohol cues. The alcohol attentional control training program (AACTP) has shown promise for retraining these biases and decreasing alcohol consumption in community samples of excessive drinkers. However, there is a lack of evidence regarding the effectiveness of ACTP in clinical AUD samples. The main aim of the present study is to investigate whether primary pharmacological and psychological, evidence-based alcohol treatment can be enhanced by the addition of a gamified AACTP smartphone application for patients with an AUD.

**Design and Methods:** The study will be implemented as a randomized controlled trial. A total of 317 consecutively enrolled patients with AUD will be recruited from alcohol outpatient clinics in Denmark. Patients will be randomized to one of three groups upon initiation of primary alcohol treatment: Group A: a gamified AACTP smartphone application + treatment as usual (TAU); Group B: a gamified AACTP sham-control application + TAU; or Group C: only TAU. Treatment outcomes will be assessed at baseline, post-treatment, and at 3- and 6-month follow-ups. Repeated measures MANOVA will be used to compare the trajectories of the groups over time on alcohol attentional bias, alcohol craving, and drinking reductions. It is hypothesized that Group A will achieve better treatment outcomes than either Group B or Group C.

**Perspectives:** Because attentional bias for alcohol cues is proportional to the amount of alcohol consumed, and these biases are not addressed within current evidence-based treatment programs, this study is expected to provide new evidence regarding the effectiveness of the gamified AACTP in a clinical population. Furthermore, due to promising results found using AACTP in community samples of excessive drinkers, there is a high probability that the AACTP treatment in this study will also be effective, thereby allowing AACTP to be readily implemented in clinical settings. Finally, we expect that this study will increase the effectiveness of evidence-based AUD treatment and introduce a new, low-cost gamified treatment targeting patients with an AUD. Overall, this study is likely to have an impact at the scientific, clinical, and societal levels.

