A power analysis (79, 80) was conducted using G^*^Power for a repeated-measures MANOVA with α = 0.05; effect size (ES) of *f* =0.20; power = 0.90; groups *k* = 3; and time-points measurements = 4. It showed that 88 participants will be required for the final analyses in each of the four cells (total *N* = 264). Prior evaluations identified *f* s of 0.30 (AB) and 0.37 (weekly mean drinking) and an *f* of 0.42 (situational confidence to resist drinking) on outcome measures for sub-clinical excessive drinkers (36). Further, in a study that used the intervention as an add-on treatment for clinical participants with a substance-use disorders other than AUD, effect sizes of *f* s = 0.33 (drug-specific AB), 0.34 (number of relapses), 0.32 (temptation to use) and 0.37 (self-confidence to resist temptation) were identified (42). Also, an unpublished study conducted with detoxified drug-abusers found *f* s of 0.39 (drug-specific AB), 0.18 (number of relapses), and 0.35 (temptation to use) (81). A second power analysis for a MANOVA with special effects and interactions was conducted to test the dosage-effect across groups (α = 0.05; EF *f*
^2^(*v*) = 0.06; power = 0.90; *k* = 3; predictors = 3; and response variables = 8), which yielded an *N* of 220. Attrition in similar studies has usually ranged from 10 to 15% (41, 42). Assuming a somewhat higher attrition rate (20%), which is not unlikely (82, 83), indicates that 317 (264 + [264·0.20]) participants should be tested at baseline for an analysis using listwise deletion of missing cases, although a multiple imputation (MI) analysis will also be conducted to verify that results converge across missing data assumptions. The projected sample size is sufficient for the planned data analyses, including mediational analyses based on Fitz and MacKinnon's guidelines (84).

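### Attentional bias is measured only twice, but the abstract and the four-time-point power calculation treat it as part of a four-occasion repeated-measures model

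*Protocol article*

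**What the plan says.** **Schedule.** The Measures section lists the experimental measures (cue-induced craving, alcohol attentional bias, action-tendency bias, inhibition bias, cognitive flexibility) and says they "will be administered at baseline and post-treatment". Its next sentence gives the clinical measures a longer schedule: alcohol consumption (primary), craving, self-efficacy and affect are also taken at the 3- and 6-month follow-ups. The section on action tendency and inhibition bias agrees, since it provides two parallel task versions to cover practice effects between those two visits.

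**Analysis.** The abstract places treatment outcomes at four assessments and says a repeated-measures MANOVA will "compare the trajectories of the groups over time on alcohol attentional bias, alcohol craving, and drinking reductions". The Statistical Analysis section describes one such model, with efficacy shown by a Time × Study Group interaction across the assessment points.

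**Power.** The calculation for that model uses three groups, f = 0.20, α = 0.05, power 0.90 and "time-points measurements = 4". It concludes that "88 participants will be required for the final analyses in each of the four cells", with a total of 264. It is not tied to a named outcome, but attentional bias effects (0.30, 0.33, 0.39) are among the prior values cited beside it.

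**The concern.** Attentional bias is the process the training targets and, with craving, a hypothesised mediator of the drinking effect. A reader of the abstract and the power paragraph would take it to be followed to six months and covered by the four-time-point calculation. By the schedule it has no follow-up values, and the calculation describes a different test.

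Two things are at stake. The abstract promises a trajectory that will not exist. And the form of the attentional bias analysis (change score, baseline-adjusted comparison, or part of a joint model) is left open because the one model described does not fit the data to be collected.

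**Working it through.** **Inputs.** From Statistical Analysis: α = 0.05, f = 0.20, k = 3 groups, m = 4 time-points, N = 264 analysed (3 × 88; the text says four cells, but there are three groups), 317 enrolled, 20% attrition. 317 × 0.8 = 253.6, so 253 to 254 completers. From Measures: m = 2 for attentional bias and the other experimental measures.

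**Method.** Within-between interaction in a repeated-measures MANOVA, Pillai trace, noncentral F:
- p = m − 1; s = min(k − 1, p); df1 = (k − 1)p; df2 = s(N − k − p + s)
- noncentrality λ = N·s·f² (O'Brien–Shieh) or λ = df2·f² (Muller–Peterson)

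**Step 1: the plan's own figure (m = 4).** p = 3, s = 2, df1 = 6. At N = 264, df2 = 2 × (264 − 3 − 3 + 2) = 520 and λ = 264 × 2 × 0.04 = 21.12 (or 520 × 0.04 = 20.80). Power is 0.950 (or 0.947). Power of 0.90 needs only N = 221 (or 225). So 264 does not reproduce as the N for 0.90; under the first convention it is exactly the smallest N for 0.95.

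**Step 2: two occasions (m = 2), same f.** p = 1, s = 1, df1 = 2. This is a one-way ANOVA on change. At N = 264, df2 = 261 and λ = 264 × 0.04 = 10.56 (or 10.44).

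| N analysed | O'Brien–Shieh | Muller–Peterson |
|---|---|---|
| 264 | 0.833 | 0.828 |
| 254 | 0.817 | 0.812 |
| 253 | 0.815 | 0.810 |
| N for 0.90 | 320 | 323 |

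**Step 3: sensitivity to f (m = 2, N = 264, O'Brien–Shieh).**

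| f | Power |
|---|---|
| 0.18 | 0.74 |
| 0.20 | 0.83 |
| 0.22 | 0.90 |
| 0.25 | 0.96 |
| 0.30 (cited for attentional bias) | 0.99 |

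Carrying f over is itself an assumption. With f² = V/(s − V), f = 0.20 at s = 2 means V = 2 × 0.04/1.04 = 0.077. The same V at s = 1 gives f = √(0.077/0.923) = 0.289 and power 0.99.

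**Step 4: baseline-adjusted ANCOVA.** With equal variances at the two visits and baseline–post correlation r, the change score has variance 2σ²(1 − r) and the ANCOVA residual σ²(1 − r²). λ is therefore multiplied by 2(1 − r)/(1 − r²). The plan gives no r, so a range is assumed, with f = 0.20 on the change scale.

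| r | Multiplier | Power, N = 264 | Power, N = 253 |
|---|---|---|---|
| 0.3 | 1.538 | 0.957 | 0.949 |
| 0.5 | 1.333 | 0.927 | 0.915 |
| 0.7 | 1.176 | 0.891 | 0.876 |

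**The case against.** The Measures section states the schedule clearly, and the model is described as running across the assessment points, which can be read as whichever points each measure has. A two-occasion Time × Group test of attentional bias is valid and fits that reading. No sentence says in terms that attentional bias is analysed at four occasions, and the power paragraph names no outcome. All of this stands. The four-occasion analysis of attentional bias is implied by the abstract and the power inputs together, and it would be wrong to say that attentional bias cannot be tested at all.

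A reader might also infer that the two-visit schedule cuts power from 0.90 to about 0.82. The document does not support that. Its own inputs give about 0.95 at N = 264, so the like-for-like comparison is 0.95 with 0.83, and even that holds only if f = 0.20 transfers to a design with a different s. At the attentional bias effects the plan cites (f = 0.30 or more, from other populations), two occasions are ample.

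Nor does it follow that mediation power is capped at this figure. The 0.83 is for a 2-df test across three groups, whereas the group-to-mediator path is usually a specific contrast, whose power may be higher or lower. Craving, the other mediator, is measured clinically at all four visits.

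Preferring ANCOVA to a change analysis is a matter of efficiency; the change test is not an error. What the objection does not remove is the conflict between the abstract, the four-time-point calculation and the two-visit schedule.

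**Conclusion.** The point holds as a mismatch between schedule and analysis for attentional bias, and any four-occasion model is equally unavailable for the other experimental measures. None of them can enter a four-occasion Time × Group test or a joint four-occasion MANOVA with drinking, and the published power calculation does not apply to them. The abstract's craving outcome can be met by the visual analog scale, which is collected four times; cue-induced craving cannot meet it. The primary outcome and its power are untouched.

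The effect on power is secondary and conditional. At f = 0.20 carried over to two occasions, a change analysis has about 0.83 at N = 264 and 0.81 to 0.82 with 253 to 254 completers, below the stated 0.90. It reaches 0.90 at f = 0.22 and 0.99 at f = 0.30. The mismatch does not depend on these figures. It is worth correcting because it concerns the main mechanistic outcome and a hypothesised mediator.

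**What to change.** 1. In Statistical Analysis, limit the four-occasion model to the measures that the Measures section schedules at all four visits: weekly drinking, visual-analog craving, self-efficacy and affect.
2. Specify one analysis for attentional bias and the other experimental measures: a post-treatment group comparison adjusted for the baseline value (ANCOVA).
3. Give these measures a separate power statement with its assumptions shown. At f = 0.20 on the change scale, the ANCOVA has about 0.88 to 0.96 for assumed baseline–post correlations of 0.7 to 0.3, across N = 253 to 264.
4. Align the abstract's assessment schedule and its sentence on trajectories with Measures, so that no follow-up course is implied for attentional bias.
5. While editing the power paragraph, reconcile the pair of 264 and 0.90, since the stated inputs give about 0.95.

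The cost is wording in the abstract and the analysis section. No visits, patients or assessments are added, and the baseline values that the ANCOVA needs are already collected.
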